# Efficacy and safety of PERIOdontal treatment versus usual care for Nonalcoholic liver disease: protocol of the PERION multicenter, two-arm, open-label, randomized trial

**DOI:** 10.1186/s13063-020-4201-y

**Published:** 2020-03-23

**Keywords:** NAFLD, *Porphyromonas gingivalis*, Periodontal treatment, Lipopolysaccharides, Alanine aminotransferase, Immunoglobulin G

## Abstract

**Background:**

We report the first protocol for a multicenter, randomized comparison study to compare the efficacies of periodontal scaling and root-planing treatment against that of tooth-brushing treatment for nonalcoholic fatty liver disease (NAFLD) (PERION: PERIOdontal treatment for NAFLD). Nonalcoholic steatohepatitis (NASH) is an advanced form of NAFLD, which can progress to cirrhosis and hepatocellular carcinoma. Increased endotoxemia is associated with the progression of NAFLD. Periodontal bacteria possess endotoxins; *Porphyromonas gingivalis* is well-known as a major pathogenic bacterium in periodontitis, and serum antibody levels for *P. gingivalis* are high in patients with periodontitis. Several reports have indicated that *P. gingivalis* is related to NAFLD. This study aims to investigate the effect of periodontal treatment for liver damage, *P. gingivalis* infection, and endotoxemia on patients with NAFLD.

**Methods:**

We will include adult patients (20–85 years old) with NAFLD, alanine aminotransferase (ALT) ≥ 40 IU/L, and equivalent steatosis grade ≥ 1 (target sample size, *n* = 40 patients; planned number of patients with outcome data, *n* = 32). Participants will be randomly assigned to one of two groups: a scaling and root-planing group or tooth-brushing as the usual group. The primary outcome will be the change in ALT levels from baseline to 12 weeks; the key secondary outcome will be the change in the serum immunoglobulin G (IgG) antibody titer for *P. gingivalis* at 12 weeks.

**Discussion:**

This study should determine whether periodontal treatment decreases liver damage, *P. gingivalis* infection, and endotoxemia in patients with NAFLD.

**Trial registration:**

University Hospital Medical Information Network (UMIN) Clinical Trials Registry, ID: UMIN000022079.

## Background

The broad spectrum of fatty liver diseases in individuals who consume little-to-no alcohol is called nonalcoholic fatty liver disease (NAFLD) and includes nonalcoholic steatohepatitis (NASH). NASH is an increasingly common cause of chronic liver disease worldwide and is associated with increased liver-related mortality and hepatocellular carcinoma [1–3]. NASH progresses to cirrhosis in 15–20% of the affected individuals and is a rising indication for liver transplantation [4]. However, approved therapies for NASH have not yet been established; therefore, preventive therapies to inhibit the progression of fatty liver disease to NASH are required.

Periodontal disease is an infectious disease of the gums and tissues surrounding the teeth and causes tooth loss resulting from the destruction of tooth-supporting tissues. The incidence rate of periodontitis is >  47% in adults in the USA [5]. More than 700 bacterial species or phylotypes have been detected in the oral cavity [6]. Some species/complexes are closely associated with advanced periodontal lesions, such as *Porphyromonas gingivalis*, *Treponema denticola*, *Tannerella forsythia*, *Prevotella intermedia*, *Fusobacterium nucleatum*, and *Aggregatibacter actinomycetemcomitans* [7, 8]. Among them, *P. gingivalis*, a gram-negative anerobic bacterium, is the major etiologic agent that contributes to periodontal disease progression and bone and tissue destruction [9, 10]. The lipopolysaccharide (LPS) cell-wall component of *P. gingivalis* is one of the virulence factors that trigger a wide range of host responses, including the production of pro-inflammatory cytokines, anti-inflammatory cytokines, and chemokines [11]. These cytokines and inflammatory mediators play important roles in the progression of periodontitis at the stage where host immune and inflammatory responses lead to the destruction of periodontal tissue under the influence of multiple behavioral, environmental, and genetic factors [12].

Recently, several studies have reported the relationship between NAFLD and periodontal disease [13, 14]. Yoneda et al. [15] reported that the detection frequency of *P. gingivalis* in the saliva of patients with NAFLD and patients with NASH was significantly higher than that in non-NAFLD control subjects. Moreover, they presented preliminary evidence to suggest that nonsurgical periodontal treatments in 10 patients with NAFLD for 3 months ameliorated the liver function parameters, such as the serum levels of aspartate aminotransferase (AST) and alanine aminotransferase (ALT). Consequently, it is thought that infection with a periodontal pathogen, mainly *P. gingivalis*, is associated with fibrosis severity in patients with NAFLD and that the prevention and elimination of *P. gingivalis* infection by periodontal treatment may have a beneficial effect on the management of NASH (Fig. 1).

**Fig. 1 Fig1:**
[figure not shown]
Schematic overview of periodontal treatment of NAFLD suppressing periodontal endotoxin. *NAFLD* nonalcoholic fatty liver disease, *TLR2/TLR4* toll-like receptors 2 and 4

Therefore, we hypothesized that the elimination of oral infection, including *P. gingivalis* infection, by periodontal treatment in patients with NAFLD would ameliorate NAFLD-related clinical markers. We performed a clinical study to confirm the preliminary finding under collaborative medical and dental care.

Thus, we have devised a prospective, multicenter, randomized comparison trial to evaluate periodontal treatment as a candidate for NAFLD treatment. This is the first protocol for a randomized comparison trial for periodontal treatment against NAFLD in humans.

## Methods

### Design

The PERION trial is designed as a prospective, multicenter, two-arm, randomized comparison study to test the efficacy of the 12-week scaling and root-planing group versus the tooth-brushing group in NAFLD with moderate periodontitis. The study will recruit 40 adults and evaluate the efficacy and safety of periodontal treatment for 60 weeks, with the primary endpoint at 12 weeks. The study design is shown in Fig. 2.

**Fig. 2 Fig2:**
[figure not shown]
Study design for PERION. Planned sample size, *N* = 32; enrolled, *N* = 40. PERION, PERIOdontal treatment for NAFLD, *NAFLD* nonalcoholic fatty liver disease

### Recruitment process and allocation

The PERION trial patient population will be derived from the Kanagawa Dental University Yokohama Clinic, Kanagawa Dental University, Iwasaki Internal Medicine Clinic, and the Yokohama City University Hospital Cohort. The randomized allocation will be conducted at Yokohama City University. Eligible patients will be screened by the principal and sub-investigator (gastroenterologists and periodontists). Patient recruitment will be performed 8 h a day, 5 days a week.

### Endpoint detection

In the short-term studies (Phases I and IIa), aimed primarily at detecting wasted signals to make direct decisions on further development, a sustained improvement in AST and ALT levels will be useful as the endpoint of PERION (Fig. 3) [16]. While the use of ALT as a surrogate marker for NAFLD is controversial, studies have shown that ALT reduction is associated with reduced hepatocyte damage and liver inflammation [17], but not steatosis [18]. Because there are no other commonly established noninvasive biomarkers for use in the NAFLD/NASH clinical trial, ALT reduction was selected as the primary endpoint of this trial. To assist the primary endpoint, several secondary endpoints were selected to assess the pathogenesis of NAFLD using noninvasive methods (Fig. 3). Therefore, the primary endpoint of PERION is set as a change in ALT levels from baseline after 12 weeks of intervention. Also, the PERION study will evaluate periodontal treatment as a candidate for the first treatment to improve NAFLD pathogenesis via decreasing *P. gingivalis* count. Therefore, the key secondary endpoint is the serum immunoglobulin G (IgG) antibody titer of *P. gingivalis* [19].

**Fig. 3 Fig3:**
[figure not shown]
Efficacy endpoints for PERION. *ALP* alkaline phosphatase, *ALT* alanine aminotransferase, *AST* aspartate aminotransferase, *BMI* body mass index, *CAP* controlled attenuation parameter, *CK-18* cytokeratin 18, *CRP* C-reactive protein, *EAA* endotoxin activity assay, *GGT* γ-glutamyltransferase, *h-CRP* high-sensitivity C-reactive protein, *HDL-C* high-density lipoprotein-cholesterol, *HOMA-IR* homeostasis model assessment of insulin resistance, *HRQOL* health-related quality of life, *IL-6* interleukin-6, *LDL-C* low-density lipoprotein-cholesterol, *M2BP* Mac-2 binding protein, *MRE* magnetic resonance elastography, *NAFLD* nonalcoholic fatty liver disease, *PERION* PERIOdontal treatment for NAFLD, *PDFF* proton density fat fraction, *SF-8* short form-8, *QOL* quality of life, *T-Bil* total bilirubin, *T-Cho* total cholesterol, *TG* triglycerides, *TNF-α* tumor necrosis factor-α, *VCTE* vibration-controlled transient elastography

### Periodontal disease examination

The subject will be examined to assess the amount of periodontal disease bacteria (*P. gingivalis,* etc.), degree of infection, and periodontal disease severity. All examinations will be performed by two periodontal disease specialists enrolled at Kanagawa Dental University Hospital and Kanagawa Dental University Yokohama Clinic. The amount of *P. gingivalis* in saliva is measured by quantitative polymerase chain reaction (qPCR), and the infection level of periodontal disease is examined using a serum IgG antibody titer test for *P. gingivalis* FDC381 by enzyme-linked immunosorbent assay (ELISA). The severity of periodontal disease will be examined by probing depths, clinical attachment levels, gingival bleedings on probing (BOP) at six sites per tooth using a calibrated periodontal probe, and the stability of the teeth.

### Periodontal treatment

The primary purpose of nonsurgical periodontal treatment is to control periodontal infection of microorganisms by removing bacterial biofilm, calculus, and toxins from the root surface. According to a review of the scientific literature, mechanical nonsurgical periodontal treatment significantly reduces the inflammation level and the probing pocket depth and increases the clinical attachment level [20]. The successful treatment of plaque-induced periodontitis will recover periodontal health, but gingival recession often occurs. At first, instruction on correct brushing of the teeth will be given to patients with periodontal disease (tooth-brushing group). Then, the removal of supra- and sub-gingival bacterial plaque/biofilm and calculus by periodontal scaling and root-planing will be performed. Quadrant/sextant-wise instrumentation (conventional staged debridement, CSD) will be performed (scaling and root-planing group).

### NAFLD treatment

We will provide standard lifestyle modification recommendations that each site can provide to the patients at the time that the informed consent document is signed. We will recommend a hypocaloric diet (daily calorie reduction of 500–1000 kcal) with reduced consumption of processed carbohydrates and fructose-containing beverages and will recommend the performance of moderate-intensity exercise for 30–45 min three to four times/week. This diet and exercise therapy will be performed without changing the prescription.

### Sample size determination

Our previous pilot study showed that nonsurgical periodontal treatments on 10 NAFLD patients for 3 months ameliorated the liver function parameters, such as the serum levels of AST and ALT [15]. It showed a mean ALT change of − 25.0 (IU/L), with a standard deviation of 25. On the basis of these data, the sample size is determined to guarantee the power of the analysis of variance *F* test. Assuming the mean changes in ALT in the no-treatment group and active treatment groups to be 0 and − 25, respectively, with a common standard deviation of 25, the required number of patients per group with a power of 80% and a two-sided significance level of 5% was calculated to be 16. We aim to recruit a total of 40 patients (scaling and root-planing treatment, 20, tooth-brushing treatment, 20) to compensate for the dropout patients.

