### Randomization

Before providing informed consent, patients will undergo a screening test as a first step to determine whether they meet the inclusion criteria for the study and none of the exclusion criteria. For patients determined to be eligible, the principal investigator or co-investigator will complete a Patient Enrollment Form with the necessary information, which is sent by fax or e-mail to the Patient Enrollment Center (Yokohama City University). The Patient Enrollment Center will then confirm the eligibility of the patient based on the enrollment form, enroll and randomize the patient, and notify the principal investigator or co-investigator of the Patient ID number and the allocation number via fax or e-mail. After an eligibility check, patients will be randomly assigned to receive periodontal treatment or no treatment at the Central Registration Center by a computer program, using a stratified block randomization method, adjusting for age (≥ 65/< 65 years) and sex (male/female). Therefore, the patient assignment is concealed from the investigator.

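### The 80% power is computed against an untreated control with zero ALT change, but the randomized comparator is tooth-brushing instruction, for which no zero change is supported

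*Protocol article*

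**What the plan says.** All places are in the protocol article.

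- **Sample size determination.** The source of the effect is a pilot in which "nonsurgical periodontal treatments on 10 NAFLD patients for 3 months ameliorated the liver function parameters". The mean ALT change there was −25 IU/L with SD 25, and no pilot control group is mentioned. The calculation proceeds by "Assuming the mean changes in ALT in the no-treatment group and active treatment groups to be 0" for the first of these; the active value is −25 IU/L. Both are taken "with a common standard deviation of 25". The stated method is that "the sample size is determined to guarantee the power of the analysis of variance" F test, and the number per group for "a power of 80% and a two-sided significance level of 5% was calculated to be 16". The section's last sentence plans 20 patients for scaling and root-planing and 20 for tooth-brushing.
- **Randomization.** Here "patients will be randomly assigned to receive periodontal treatment or no treatment".
- **Abstract and Design.** Both give the comparator as tooth-brushing.
- **Periodontal treatment.** At first, "instruction on correct brushing of the teeth will be given to patients with periodontal disease (tooth-brushing group"); removal of plaque and calculus by scaling and root-planing then follows.
- **NAFLD treatment.** The sites recommend a reduced-calorie diet and "will recommend the performance of moderate-intensity exercise", without limiting this to one arm.
- **Table 1.** Patients must have an ALT above 40 IU/L and must not have responded to three months of diet and exercise.

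**The concern.** The calculation and the Randomization section describe an untreated control. The rest of the article, including the last sentence of the sample size section itself, describes an arm that receives brushing instruction.

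The mismatch reaches the effect size. Using a single-arm change of −25 as the between-arm difference requires the comparator arm to change by exactly zero. As the Periodontal treatment section is written, brushing instruction is the first step of the care that scaling and root-planing completes. Any ALT benefit from that step would therefore be present in both arms and drop out of the contrast. The article offers no reason to set it at zero.

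At stake is the stated power. If the comparator arm improves at all while the active arm improves by 25, the trial has less than 80% power for the comparison it makes, and a reader of the article cannot see how much less.

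**Working it through.** **Inputs** (Sample size determination): two-sided α = 0.05, power 80%, mean changes 0 and −25 IU/L, common SD σ = 25, 16 evaluable per group, 20 enrolled per group.

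**1. The plan's own figure.** By the normal approximation, n = 2(1.960 + 0.842)² σ²/Δ². With σ = Δ = 25 this is 2 × 7.85 = 15.7, so 16 per group. The stated number reproduces, with power 80.7% on that approximation.

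**2. The test that the section names.** With two groups the F test equals the two-sample t test. Its exact power comes from the noncentral t distribution with 2n − 2 degrees of freedom and noncentrality (Δ/σ)√(n/2). At n = 16 and Δ = 25 the noncentrality is √8 = 2.83 and power is 78.1%; at n = 17 it is 80.7%. The F test therefore needs 17 per group for 80%.

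**3. The planned primary test.** The Statistical analyses section specifies a Wilcoxon test. Read as a two-sample rank-sum test and simulated with normal data, 16 per group and SD 25, its power is about 75% at a net difference of 25, 55% at 20 and 35% at 15.

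**4. Power when the comparator arm also changes.** The article gives no ALT change for tooth-brushing, so the falls below are assumptions shown as a range. The active arm is held at −25 and SD at 25 (exact t).

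| Assumed comparator fall (IU/L) | Net difference (IU/L) | Power, 16 per group | Power, 20 per group | Evaluable per group for 80% |
|---|---|---|---|---|
| 0 | 25 | 78% | 87% | 17 |
| 5 | 20 | 59% | 69% | 26 |
| 10 | 15 | 38% | 46% | 45 |

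The 20-per-group column applies only if every enrolled patient is evaluable.

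**5. Difference with 80% power.** Solving the same equation for Δ gives 25.6 IU/L with 16 per group and 22.7 IU/L with 20 per group.

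**6. Precision of the pilot change.** If the pilot SD of 25 is the SD of the change, the 95% interval is 25 ± 2.262 × 25/√10 = 25 ± 17.9, a fall of about 7 to 43 IU/L. The planning value is imprecise even before any comparator change is considered.

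**7. Smallest observed difference that is significant.** The standard error is 25√(2/16) = 8.84 and the critical t on 30 degrees of freedom is 2.04. An observed difference of about 18 IU/L already reaches p = 0.05.

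**The case against.** The strongest reply is that nothing has been miscalculated: 16 per group follows from the stated inputs, and the article does not show that the comparator arm changes by anything other than zero. That stands. Zero is unsupported, not refuted, and the 59% and 38% are consequences of assumed falls.

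A reader might also infer that diet and exercise advice, or regression to the mean after entry on a raised ALT, must erode the contrast. The documents do not support this. Both act on the two arms alike and cancel in the difference. They lower power only to the extent that the pilot's −25 already contains them, and the article describes neither the pilot's background advice nor its entry rule. The requirement of prior non-response to diet and exercise in Table 1 argues for a small diet effect. The brushing argument does not depend on either route.

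A reader might further infer that the trial can detect nothing smaller than the whole pilot change. That confuses the difference with 80% power (25.6 IU/L) with the smallest significant observed difference (about 18 IU/L). On the exact t calculation, a true difference of 20 is found 59% of the time.

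Finally, the article already plans 95% confidence intervals, lists the small sample as its first limitation and calls the approach proof-of-concept. This softens the risk of misreading a null result, and nowhere does the article say that such a result will be taken as no effect. It does not tell the reader that the power was computed for a different comparator. The correct arm name at the end of the sample size section shows the contradiction but does not resolve it.

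**Conclusion.** The point holds in a limited form. The 80% was computed for active treatment against an untreated arm with zero change; the trial compares scaling and root-planing with tooth-brushing instruction, and no text supports zero for that arm. Two sections name a control that the trial does not have.

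The part of the size that needs no assumption about the comparator's change is small: at the planned net difference of 25 IU/L, power is 78% by the named F test and, under normality, about 75% by Wilcoxon. The larger loss, to 59% at a net 20 and 38% at a net 15, is conditional on comparator falls of 5 and 10 IU/L, an active change of −25, SD 25 and 16 evaluable per group. The article makes none of these falls more likely than zero. The stated power is therefore unsupported, not shown to be wrong.

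**What to change.** 1. In Sample size determination and in Randomization, replace the untreated control with the tooth-brushing comparator, so that they agree with the Abstract, Design and Periodontal treatment sections.
2. Restate the calculation as a net between-arm difference. State the ALT change expected under tooth-brushing and the reason for it or, failing a source, give power at net differences of 25, 20 and 15 IU/L: about 78%, 59% and 38% with 16 per group, and 87%, 69% and 46% if all 20 per group are evaluable. Label this as a range under assumption.
3. Give the difference that has 80% power: about 26 IU/L with 16 per group, about 23 IU/L with 20.
4. Say that 16 comes from the normal approximation and that the F test needs 17.

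The cost is a few changed sentences, a short table and a less favourable stated power. It needs no added patients and no change to the analysis.

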### Statistical analyses

The Full Analysis Set (FAS) will be the primary analysis set for efficacy. We define FAS to include any subjects who receive any amount of the study medication without a lack of information on the primary endpoint (complete case analysis). For the blood liver function test using ALT, the summary statistics (mean, standard deviation) will be calculated at baseline and 12 weeks. Details of the statistical design will be described in the Statistical Analysis Plan. In this study, statistical analysis will be performed mainly for the following items. For the primary analysis, (ALT after treatment – ALT at baseline) will be sought for each subject and the corresponding Wilcoxon test will be performed. The significance level will be 5% on both sides. In addition to *p* values, we will provide point estimates with 95% confidence intervals. As a sensitivity analysis, the two groups would be compared using the analysis of covariance using the primary endpoint as an outcome, adjusting for ALT at baseline as a covariate. For the key secondary endpoint, *P. gingivalis* IgG antibody titer in the blood (values after treatment – values at baseline) will be sought for each subject and the paired Wilcoxon test will be performed. Subgroup analysis will be conducted. Stratified analysis will be performed using *P. gingivalis* bacterial content, proton density fat fraction (PDFF), magnetic resonance elastography (MRE), and periodontal pocket as indices. Stratified analysis will be performed using above/below the median of *P. gingivalis* bacterial content, endotoxin, PDFF, MRE, and periodontal pocket depth. We hypotheses a larger reduction in ALT with the intervention in the patient group with high *P. gingivalis* bacterial content, high endotoxin levels, high PDFF, low MRE, and deep periodontal pockets at baseline. Therefore, we conducted multivariable linear regression with difference in ALT between groups as dependent variable and at least the treatment group, the respective subgroup variable (categorized), and the interaction term (treatment group×subgroup variable) as independent variables. The significance level will be 5% on both sides. In addition to p values, we will provide point estimates with 95% confidence intervals. As a sensitivity analysis, the two groups will be compared using analysis of covariance using the key secondary endpoint as an outcome adjusting for *P. gingivalis* IgG antibody titer at baseline as a covariate. As the safety analysis, the incidence and severity of AEs and reactions will be calculated.

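### The 16 per group comes from a normal approximation: exact power is 78% for the F test named, and about 75% for the primary Wilcoxon test if it is a rank-sum test and ALT changes are normal

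*Protocol article*

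**What the plan says.** Under Sample size determination, the protocol article names the test that the calculation serves: "the sample size is determined to guarantee the power of the analysis of variance *F* test". The expected changes are given as "Assuming the mean changes in ALT in the no-treatment group and active treatment groups to be 0 and − 25, respectively". Both arms share an SD of 25 IU/L. The result is "the required number of patients per group with a power of 80% and a two-sided significance level of 5% was calculated to be 16". Recruitment is set at 20 per arm to cover dropout. The Abstract and the Fig. 2 caption both plan on 32 patients with outcome data out of 40.

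Under Statistical analyses, the primary analysis takes each patient's change in ALT from baseline and says that "the corresponding Wilcoxon test will be performed", with "The significance level will be 5% on both sides". The only parametric comparison of the two groups on ALT change is an analysis of covariance adjusted for baseline ALT, and it is a sensitivity analysis. The primary analysis set is complete-case. For the key secondary endpoint the same section specifies a paired Wilcoxon test; for ALT it does not say whether the test is paired or two-sample.

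**The concern.** The sizing section names one test and the analysis section uses another, and the article gives no power for the test that decides the trial. The stated 80% should belong either to the F test or to the Wilcoxon test. If it belongs to neither, the article's only stated power figure is too high at its own planned number of evaluable patients.

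Two things are at stake. A null result would be judged against an 80% chance of detecting the assumed effect when the real chance may be lower. The dropout allowance also depends on the figure: 16 of 20 per arm tolerates 20% loss, and a larger evaluable number leaves less room.

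**Working it through.** **Inputs** (Sample size determination): difference Δ = 0 − (−25) = 25 IU/L; SD σ = 25; standardised difference d = 25/25 = 1; two-sided α = 0.05; target power 80%; equal arms. The two-sided 5% level is repeated under Statistical analyses.

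**Step 1. Reproduce the stated 16.** Large-sample normal formula:

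n per group = 2 (z₀.₉₇₅ + z₀.₈₀)² (σ/Δ)² = 2 (1.960 + 0.842)² × 1² = 15.7, rounded up to 16.

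The power by the same approximation at n = 16 is 80.7%. The stated figure therefore reproduces, and this formula is probably its source.

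**Step 2. The F test that the section names.** With two groups the F test is the two-sided t test. Exact power uses the noncentral t distribution with 2n − 2 degrees of freedom and noncentrality d√(n/2).

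- n = 16: noncentrality √8 = 2.83, 30 df, power 78.1%
- n = 17: noncentrality √8.5 = 2.92, 32 df, power 80.7%

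The named test needs 17 per group, one more than stated.

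**Step 3. The Wilcoxon test.** Two assumptions that the article does not state are needed: the test is the between-group rank-sum test, and changes are normal in each arm with a shift of 1 SD. Power was simulated with exact critical values (400,000 trials per row). The F test is shown beside it.

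| Evaluable per group | F test, exact | Rank-sum, normal changes |
|---|---|---|
| 16 | 78.1% | 75.0% |
| 17 | 80.7% | 78.4% |
| 18 | 83.0% | 80.4% |
| 20 | 86.9% | 85.0% |

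A rough check scales n by the large-sample efficiency 3/π of the rank-sum test and gives 76.1% at 16. The Noether formula gives 72.2%. Both are close to the simulated value. Under these assumptions 80% needs 18 per group.

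**Step 4. Split the shortfall at 16 per group.** From the stated 80% to the exact F test: 80 − 78.1 = 1.9 points, due to the normal approximation. From the F test to the rank-sum test: 78.1 − 75.0 = 3.1 points, due to the change of test.

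**Step 5. Sensitivity to the shape of the changes.** Rank-sum power at 16 per group with the same difference and SD:

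| Shape | Power |
|---|---|
| Uniform | 70% |
| Normal | 75% |
| t, 5 df | 83% |
| Shifted exponential | 91% |
| t, 3 df | 93% |

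**Step 6. Dropout.** 16 of 20 per arm is (20 − 16)/20 = 20% loss; 18 of 20 is (20 − 18)/20 = 10% loss.

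**Step 7. Baseline-adjusted ANCOVA at 16 per group.** The article gives no correlation ρ between baseline and 12-week ALT, so ρ is an assumption here, as are normal data and equal variances at the two times. The SD of change is then s√(2(1 − ρ)) and the residual SD after adjustment is s√(1 − ρ²), where s is the SD at each time. Their ratio gives residual SD = 25√((1 + ρ)/2).

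- ρ = 0.5: 25√0.75 = 21.7, so d = 25/21.7 = 1.15; power about 87%
- ρ = 0.7: 25√0.85 = 23.0, so d = 25/23.0 = 1.08; power about 83%

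These powers use 29 df and average over chance baseline imbalance; ignoring imbalance gives about 88% and 84%.

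**The case against.** The strongest reply is that nothing was miscalculated. The normal formula is a standard approximation, it returns 16, and the exact F test differs by one patient per group. That stands: the 16 is an approximation. But the article attaches the 80% to the F test, and the exact F test does not reach it at 16.

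A second reply is that 75% is only one scenario. The article states no distribution for ALT change, and a rank test may have been chosen because skewness was expected. This also stands in part. A reader might infer that the switch to the Wilcoxon test by itself brings power from 80% down to 75%, or that the type II error simply is 25%. The documents support neither. About 2 of the 5 points are already lost with the F test, and the remaining 3 depend on normal changes and on a rank-sum reading of the primary test. Heavier tails or skewness can lift power above 80%, and a flat distribution lowers it to 70%. This does not confirm the stated 80%, because the article gives no shape that would justify it.

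Third, 20 per arm are recruited, and with no loss the rank-sum test has 85% power under normal changes. That is correct, but 32 patients with outcome data is the article's own planning case and the primary analysis set is complete-case, so 16 per group is the relevant number.

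Finally, a gap of 3 to 5 points is small beside the uncertainty in an effect and SD taken from 10 pilot patients. That is fair, and it limits the weight of the point. It does not make the stated figure right.

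**Conclusion.** The stated 80% at 16 per group is not what the named F test delivers: its exact power is 78.1%, and it needs 17 per group. This part depends only on the article's inputs and the usual F-test model. The primary test is a Wilcoxon test. If it is the two-sample rank-sum test and changes are normal, it does not deliver 80% either: power is about 75%, and 18 evaluable per group are needed, so tolerated loss is 10% instead of 20%. The direction of the Wilcoxon part is not fixed without a distributional assumption.

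The point is modest in size but should be corrected, because the sizing and the primary test are both fixed in this article and do not match. It does not show that the trial is too small. The planned recruitment can still give 80% or more with the rank-sum test if at least 18 per arm are evaluable.

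**What to change.** Restate the power in Sample size determination along these lines: *With 16 evaluable patients per group, power is 78% for the F test and about 75% for the Wilcoxon rank-sum test if changes are normally distributed; 80% with the rank-sum test needs 18 evaluable per group.* In Statistical analyses, state that the primary Wilcoxon test is the two-sample rank-sum test comparing the arms.

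As an option, make the baseline-adjusted ANCOVA, already planned as a sensitivity analysis, the primary analysis, and state its power with the baseline correlation shown as an assumption (about 83% to 87% at 16 per group for correlations of 0.7 to 0.5).

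No extra patients are needed. The cost is an edit to two sections and, unless ANCOVA is adopted, a slightly less favourable stated power and a dropout allowance of 10% for 80% power with the rank-sum test.
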